**Fig. 3 Fig3:**
[figure not shown]
Supportive Oncology Care at Home for Hospitalized Patients with Cancer Consort Diagram

#### Participant selection

To be eligible, patients must be (1) age 18 or older; (2) diagnosed with advanced cancer (defined as receiving treatment with palliative intent per chemotherapy order entry treatment intent designation and/or trial consent form or based on documentation in the oncology clinic notes for those not receiving chemotherapy); (3) admitted with an unplanned hospitalization at MGH; (4) not requiring intensive care unit-level care during their hospitalization; (5) verbally fluent in English; and (6) residing in the state of Massachusetts within approximately 50 miles of MGH. We will exclude patients who are (1) admitted to the intensive care unit; (2) have a high oxygen requirement (e.g., FiO2 > 0.40); (3) experience active angina or cardiac arrythmias during admission; (4) have a planned inpatient surgical or interventional procedure; (5) have uncontrolled psychiatric illness or impaired cognition interfering with their ability to understand study procedures and provide informed consent; (6) are deemed ineligible for home-based acute care based on the inpatient oncology clinician assessment; or (7) are planning to be discharged to hospice or to any location other than home.

Eligible patients may also identify caregivers for study participation. Caregivers must be (1) a relative or friend of eligible patient; (2) verbally fluent in English; and (3) age 18 or older. Patients without an available caregiver are still eligible to participate. The goal of this study entails assessing the acceptability of this care model, and thus we will also enroll the outpatient oncology physicians and advance practice clinicians who care for patients receiving Supportive Oncology Care at Home to obtain information regarding their perceptions of the intervention.

#### Enrollment

We will identify patients for study participation by screening the inpatient oncology census on a daily basis. We will recruit patients hospitalized at MGH within 72 h or three business days of admission. The study team will email the inpatient oncology team to request permission to approach potentially eligible patients for study participation. If the oncology clinician has no objections, the study team will approach the patient in-person or over the phone and obtain informed consent. Patients will then be asked to complete baseline assessment. We will ask patients interested in participating in the study to identify a caregiver upon whom they rely for help who might be willing to participate in the study. Caregivers will be eligible to enroll either at the same time as the patient, or within seven days of obtaining informed consent from the patient. Within one month of their patient completing the Supportive Oncology Care at Home intervention, study staff will meet with eligible clinicians, introduce them to the study, and obtain consent in a private setting.

#### Supportive oncology care at home intervention

Figure 1 depicts the Supportive Oncology Care at Home intervention as noted above. Participants will receive the intervention for a defined period of days to weeks (modified based on patient and clinician feedback) after their discharge from the hospital to reduce the risk of rehospitalization. Participants on study will continue to receive their standard oncology care and attend their regular clinic visits.

#### Study outcomes

The primary endpoint of this trial is feasibility. The proposed intervention will be deemed feasible if (1) at least 60% of eligible patients agree to participate in the study and (2) participants complete at least 60% of their daily assessments (i.e., patient-reported symptoms, vital signs, and body weight). Secondary endpoints include additional feasibility and acceptability metrics as well as participant-reported outcomes and healthcare utilization as depicted in Table 2. We will collect participant-reported outcomes at baseline and subsequent weeks post-enrollment.

**Table 2 Tab2:** Supportive Oncology Care at Home for Hospitalized Patients with Cancer Study Outcomes

Study Outcomes
**Feasibility**
Proportion of patients who agree to participate in the study (goal at least 60%) **(primary)**
Proportion of daily assessments completed (goals at least 60%) **(primary)**
Number of home visits required, their average duration, the issues addressed at home, and the interventions delivered to patients at their home
Number of phone calls required per patient and their average duration
Number of emails from Medically Home to the primary oncology team
**Acceptability**
Acceptability ratings from patients, caregivers, and clinicians
Exit qualitative interviews with patients, caregivers, and their clinicians
**Health Care Utilization**
Index hospitalization length of stay
Proportion of days patients spent outside the hospital during the study period
Patients needing an urgent clinic visit (yes vs. no) and number of urgent clinic visits in the month post-enrollment
Patients needing an ED visit and number of ED visits in the month post-enrollment
Patients needing a hospitalization and number of hospitalizations in the month post-enrollment
Proportion of patients needing an urgent clinic visit, ED visit, or a hospitalization in the month post-enrollment
Hospitalization length of stay in the month post-enrollment

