**Health Care Utilization**
Proportion of patients requiring a hospitalization in the lats week and month of life
Number of hospitalizations in the last month of life
Proportion of patients needing an urgent clinic visit in the last month of life
Number of urgent clinic visits in the last month of life
Proportion of patients needing an ED visit in the last month of life
Number of ED visits in the last month of life
Death location
Proportion of days patients spend outside of the hospital or clinic in the last month of life
Proportion of patients needing an urgent clinic visit, ED visit, or a hospitalization throughout the study period

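### Study 2 starts the one-month clock for five utilization outcomes at inpatient enrolment, not at discharge, so part of the month at risk of readmission is lost

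*Protocol article*

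**What the plan says.** Timing of enrolment (Study #2, Enrollment): "We will recruit patients hospitalized at MGH within 72 h or three business days of admission". Candidates are found from the daily inpatient census, so a participant is in hospital when follow-up begins.

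Timing and aim of the intervention (Study #2, Supportive oncology care at home intervention): it is delivered "after their discharge from the hospital to reduce the risk of rehospitalization". Its length is left open: "Participants will receive the intervention for a defined period of days to weeks (modified based on patient and clinician feedback").

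Outcome windows (Study #2, Table 2, Health Care Utilization): of seven rows, five are counted over the month after enrolment. They are urgent clinic visits, ED visits, hospitalizations ("Patients needing a hospitalization and number of hospitalizations in the month post-enrollment"), the composite of these, and "Hospitalization length of stay in the month post-enrollment". Of the other two rows, one is "Index hospitalization length of stay". The other is the proportion of days outside the hospital, which refers to the study period; the article does not define when that period starts in Study 2.

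The Background cites a readmission rate of over 40% within 90 days, counted from discharge.

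**The concern.** The stated window does not match the stated aim. The intervention is meant to act on what happens after discharge, but the month starts while the patient is still an inpatient. During the rest of the index stay the patient cannot be readmitted and cannot come to the ED or an urgent clinic visit from home. Those days use up follow-up without any possibility of an event.

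The loss differs between patients: the longer the remaining index stay, the shorter the time at risk. Study 2 has a single arm, so no concurrent control group loses time in the same way, and the missing time at risk reads as lower post-discharge use. The resulting figure also has a different time origin from the discharge-based rate in the Background.

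A second, smaller matter concerns length of stay. Taken literally, hospital days in the month after enrolment include the remaining index days, which are also part of the separate index length-of-stay row. The article does not say that they are excluded.

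**Working it through.** No figure stated in the plan depends on this point. The 30 patients were chosen on the feasibility of completing the project, so there is no power or event calculation to reproduce. The check below is an illustration.

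**Inputs**
- Readmission within 90 days of discharge: 40% (Background, which says over 40%).
- Sample size: 30 (Study #2, Study design/objectives).
- One month is taken as 30 days (assumption).
- L, the index days remaining after enrolment: not given. Shown for 0, 3, 5 and 7 days (assumption).
- Constant hazard of readmission after discharge; death ignored (assumptions).

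**Formulas**
- Days at risk after discharge = 30 − L.
- Probability of readmission over d days = 1 − 0.60^(d/90).
- Relative change = that probability divided by its value at d = 30, minus 1.

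**Results**

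| L (days) | Days at risk | Recorded risk | Relative change | Expected readmitted of 30 |
|---|---|---|---|---|
| 0 | 30 | 15.7% | 0% | 4.7 |
| 3 | 27 | 14.2% | −9% | 4.3 |
| 5 | 25 | 13.2% | −16% | 4.0 |
| 7 | 23 | 12.2% | −22% | 3.7 |

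Worked line for L = 5: d = 30 − 5 = 25, and 1 − 0.60^(25/90) = 13.2%. Against 15.7% this is about 16% lower. For 30 patients, 30 × 0.132 = 4.0 compared with 30 × 0.157 = 4.7.

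With the window started at discharge, d = 30 for every patient who survives the window, and the illustrative risk is 15.7% whatever the value of L.

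**Length of stay.** On the literal reading, a patient with L = 5 and no readmission would contribute 5 hospital days to the month after enrolment, and the same 5 days would be part of the index stay. If index days are excluded, the contribution is 0. The text does not settle which is meant.

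**The case against.** The strongest case on the other side has five parts.

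**Enrolment is a legitimate time zero.** The table labels the window openly, and starting at enrolment keeps every enrolled patient. Starting at discharge conditions on a later event and leaves anyone who dies in hospital, or does not go home, without a window. This stands as a cost of the change. It does not restore the lost time at risk, because the stated purpose of the intervention lies after discharge.

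**The effect is small.** On the illustrative model the loss at L = 7 is 4.7 − 3.7 = 1.0 patient of 30, and at L = 5 it is 0.7. The binomial standard deviation is √(30 × 0.157 × 0.843), about 2.0. If readmission risk is highest soon after discharge, the days lost, which are the last of the 30, carry less risk and the understatement shrinks. This stands.

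**Index days may not enter the outcomes at all.** A reader might infer that they do throughout. The documents do not say so. In the hospitalization row, index days add no event unless the index admission itself is counted, which nothing states. The separate index length-of-stay row is compatible with index days being kept apart. The days-outside row is not tied to enrolment, so a ceiling on it cannot be derived without assuming a window. What remains is that the article does not exclude index days from the length-of-stay row.

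**Use of the results.** A reader might infer that these rates will plan a later trial or be compared with the Background figure. No section says either. A 30-day rate would in any case differ from a 90-day rate in length as well as in origin.

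**Study 3.** A reader might extend the point to its outcomes over the last month of life, since that month can begin before enrolment. That is not an error. The measures match how Study #3 frames the problem in its design section, and Table 3 also has a composite over the whole study period. The article gives no survival figure from which to size the overlap.

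**Conclusion.** The point holds for the five rows of Table 2 in Study 2 that are counted over the month after enrolment. Post-discharge time at risk is a month minus the remaining index stay, so post-discharge use is understated by an amount that varies between patients. This follows from the timing of enrolment, the timing of the intervention and the table's own windows.

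The size is uncertain. With L between 0 and 7 days, 40% readmission at 90 days and a constant hazard, the relative understatement runs from 0% to 22%. L and the hazard shape are assumptions, and the loss is nil for a patient discharged on the day of enrolment.

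For the length-of-stay row there is also an ambiguity to resolve about index days; the text does not establish double counting.

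The consequence is limited to descriptive secondary outcomes. No test or decision threshold is attached to them, and both feasibility criteria are untouched.

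**What to change.** In Table 2 of Study 2:

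1. Count hospitalizations, ED visits, urgent clinic visits, the composite and length of stay over 30 days from discharge. Alternatively, keep the present follow-up and report events per post-discharge day at risk.
2. State that index days are excluded from these five rows, and continue to report index length of stay separately.
3. Report the number of enrolled patients who die in hospital or are not discharged home, since they have no post-discharge window, and keep the enrolment-based figures as a supplementary result so that every enrolled patient appears somewhere.

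The cost is a change of wording in one table. With the discharge-based window, follow-up lengthens by each patient's remaining index stay, from the same records. Sample size, the feasibility endpoint and delivery of the intervention do not change. Study 3 needs no change on this account.

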**Patient-reported outcomes**
Changes in symptom burden (ESAS) longitudinally throughout the study
Changes in QOL (FACT-G) longitudinally throughout the study
Changes in psychological distress (HADS) longitudinally throughout the study
Changes in care satisfaction (FAMCARE) longitudinally throughout the study
Changes in self-efficacy (PROMIS measures)
**Caregiver-reported outcomes**
Changes in caregiver QOL (CarGOQoL) longitudinally throughout the study
Changes in caregiving burden (CRA) longitudinally throughout the study

#### Sample size calculation

The primary endpoint of the proposed study is feasibility. We chose the sample size for this study based on the feasibility of completing the project during the appropriate timeframe. The proposed intervention will be deemed feasible if at least 60% of eligible patients will agree to participate and if participants complete at least 60% of daily patient-reported assessments during the study periods. These estimates are informed by our prior work in this population and consistent with other feasibility studies.

### Study #3: optimize end-of-life (EOL) care at home for patients with hematologic malignancies

#### Study design/objectives

There is a critical need to optimize EOL care in patients with hematologic malignancies, as data suggest that many patients with hematologic malignancies may not receive high quality EOL care [43–45]. Specifically, patients are often hospitalized during the last month of life and frequently die in the hospital [43–45]. Moreover, many patients die in the intensive care unit and receive chemotherapy during the last month of life [43–45]. Several barriers to optimizing EOL care in this population exist, including (1) the unique clinical circumstances, such as the high level of prognostic uncertainty and the intensity of therapy offered; (2) the rapid decline in patients’ health status at the EOL with unique complications such as bleeding/cytopenias and infections requiring intensive supportive care measures that are difficult to deliver at home; and (3) an insufficient exposure of hospice clinicians to patients with hematologic malignancies, which may limit their expertise in addressing patients’ EOL issues [43–48]. Thus, new models of EOL care delivery are needed to adequately meet the needs of this population and overcome barriers to optimizing their EOL care.

We are conducting a single-arm pilot study to evaluate the feasibility and acceptability of the Optimize EOL Care at Home intervention for patients with advanced hematologic malignancies and their caregivers (Fig. 4) (NCT04690205; DFCI Protocol Number:20–468). The specific aims of the trial are as follows: (1) to evaluate the feasibility of implementing Optimize EOL Care at Home for patients with advanced hematologic malignancies; (2) to determine the acceptability of Optimize EOL Care at Home for patients, caregivers, and clinicians; (3) to describe patient-reported outcomes and healthcare utilization at the EOL for patients with advanced hematologic malignancies receiving the intervention; and (4) to describe caregiver-reported outcomes and satisfaction with patients’ EOL care for caregivers of patients receiving the intervention. We are recruiting patients at MGH in Boston and MGH community affiliates (e.g., MGH Newton-Wellesley, MGH North Shore, MGH Waltham). This study is approved by the DF/HCC Institutional Review Board.

**Fig. 4 Fig4:**
[figure not shown]
Optimize EOL Care for Patients with Hematologic Malignancies Consort Diagram

#### Participant selection

Eligibility criteria include (1) age 18 or older; (2) diagnosed with relapsed or refractory hematologic malignancy; (3) receiving treatment with non-curative intent or supportive care alone based on the intent of chemotherapy as reported in order entry or the Electronic Health Record; (4) deemed eligible to receive EOL care at home based on the primary oncologist’s assessment; (5) able to communicate and respond to questionnaires in English or with the assistance of an interpreter; and (6) residing in-state, within approximately 50 miles of MGH. Of note, patients requiring supportive transfusions in the oncology clinic will be eligible to participate. We will exclude patients with uncontrolled psychiatric illness or impaired cognition interfering with their ability to understand study procedures and provide informed consent, as determined by the primary oncologist.

Eligible patients may also identify caregivers for study participation. Caregivers must be (1) a relative or friend of eligible patient; (2) verbally fluent in English; (3) age 18 or older; and (4) involved in the care of patients near the EOL. Patients without an available caregiver are still eligible to participate. Thus, up to 30 caregivers can participate in the study. Our goal is to assess the acceptability of this care model, and we will therefore enroll the outpatient oncology physicians and advance practice clinicians who care for patients receiving the Optimize EOL Care at Home intervention to obtain their feedback on the intervention.

#### Enrollment

Patient recruitment will rely primarily on referral from oncology clinicians caring for patients with hematologic malignancies. Study staff will attend the weekly team meetings for the lymphoma, leukemia, myeloma, and stem cell transplantation and cellular therapy teams to ensure that eligible patients are identified in a timely fashion. Study staff will inquire during the team meetings regarding any potential patients who might be eligible for the study. The oncology team will then introduce the study to the patient. Subsequently, the study team will approach the patient in-person or over the phone and obtain informed consent. We will then ask patients to complete baseline assessments. We will ask patients interested in participating in the study to identify a caregiver upon whom they rely for help who might be willing to participate in the study. Caregivers will be eligible to enroll either at the same time as the patient, or within seven days of patient consent.

Within one month of study completion, study staff will meet with eligible clinicians, introduce them to the study, and obtain consent in a private setting. We anticipate approximately 15 clinicians will participate in the study.

#### Optimize eol care at home intervention

The Optimize EOL Care at Home intervention components are similar to those described above in Fig. 1. Participants will receive the intervention from the time of enrollment until death. This population experiences a substantial care burden, and thus we will only obtain daily patient-reported symptom assessments. The vital signs and body weight assessments will be utilized as needed based on the Medically Home clinicians’ assessments. Patients are permitted to attend their oncology visits, receive supportive transfusions, or palliative chemotherapy without any restrictions on the care provided by the oncology team. For patients receiving the intervention who transition to receive full hospice services, the Medically Home team will provide hospice services as part of their care in collaboration a hospice program.

#### Study outcomes

The primary endpoint of this trial is feasibility. The proposed intervention will be deemed feasible if (1) at least 60% of eligible patients agree to participate in the study and (2) at least 80% of enrolled participants complete a minimum of 60% of their daily patient-reported symptoms. Secondary endpoints include additional feasibility and acceptability metrics as well as participant-reported outcomes and healthcare utilization as depicted in Table 3. Participant-reported outcomes will be collected longitudinally every three weeks throughout the study period.

**Table 3 Tab3:** Optimize EOL Care for Patients with Hematologic Malignancies Study Outcomes

Study Outcomes
**Feasibility**
Proportion of patients who agree to participate in the study (goal at least 60%) **(primary)**
Proportion of participants who complete a minimum of 60% of their daily patient-reported assessments (goal at least 80%) **(primary)**
Number of home visits required, their average duration, the issues addressed at home, and the interventions delivered to patients at their home
Number of phone calls required per patient and their average duration
Number of emails from Medically Home to the primary oncology team
**Acceptability**
Acceptability ratings from patients, caregivers, and clinicians
Exit qualitative interviews with patients, caregivers, and their clinicians
**Health Care Utilization**
Proportion of patients requiring a hospitalization in the lats week and month of life
Number of hospitalizations in the last month of life
Proportion of patients needing an urgent clinic visit in the last month of life
Number of urgent clinic visits in the last month of life
Proportion of patients needing an ED visit in the last month of life
Number of ED visits in the last month of life
Death location
Proportion of days patients spend outside of the hospital or clinic in the last month of life
Proportion of patients needing an urgent clinic visit, ED visit, or a hospitalization throughout the study period
**Patient-reported outcomes**
Changes in symptom burden (ESAS) longitudinally throughout the study
Changes in QOL (FACT-G) longitudinally throughout the study
Changes in psychological distress (HADS) longitudinally throughout the study
**Caregiver-reported outcomes**
Changes in caregiver QOL (CarGOQoL) longitudinally throughout the study
Changes in caregiving burden (CRA) longitudinally throughout the study
Changes in psychological distress (HADS) longitudinally throughout the study
Caregiver satisfaction with patient’s EO care (FAMCARE)

